##### Diagnostic interview

The **Anxiety and Related Disorders Interview Schedule for DSM-5** (ADIS-5) [54] is a semistructured interview designed to assess DSM-5 diagnostic criteria for anxiety disorders and comorbid mental disorders (e.g., mood disorders, substance use). The interviewer determines the presence of symptoms and rates their clinical severity (CSR) on a scale from 0 (no symptoms) to 8 (extremely severe symptoms) with increasing values indicating increased distress/interference, and a clinical threshold of 4 or higher. The ADIS-5 is initially used to assess eligibility criteria for the study. Co-occurring mild to moderate major depression, obsessive-compulsive disorder or posttraumatic stress disorder are permitted at the following conditions: a) CSR of 6 or lower; b) CSR at least one-point lower than for the principal anxiety disorder. The ADIS-5 will also be used to examine treatment outcomes through the dimensional CSR scales for each mental disorder. The clinician-rated measure of outcomes will be based on the CSR of the ADIS-5 [54] for the principal anxiety disorder. While there are no data on the psychometric properties of the ADIS-5, the ADIS-IV was shown to have good interrater reliability when assessing the presence of mental disorders [4]. Interrater reliability will be assessed for 25% of audio-recorded ADIS-5 diagnostic interviews at each assessment period by randomly selected clinical evaluators.

The initial interview also comprises a clinician-administered questionnaire on sociodemographic data, and a brief structured interview on health care costs used in previous studies [32] to obtain information on mental health consultations (e.g., type of professional, duration, costs), psychotropic medication (name, dosage, length of time), indirect costs (e.g., absenteeism) and other related variables such as previous therapy experience and treatment preference. The questionnaire also examines work performance based on the short version of the **World Health Organization Health and Work Performance Questionnaire** (HPQ) [60].

##### Primary outcome measures

Two primary outcome measures are included in the study to represent self-reported anxiety symptoms as well as clinician-rated assessment for the principal anxiety disorder diagnosis. As a self-reported generic measure of anxiety symptoms, we use the **Beck Anxiety Inventory** (BAI) [61, 62]. The BAI is a 21-item measure of emotional, physiological and cognitive symptoms of anxiety that can be used in primary care patients with different anxiety disorders. With scores ranging from 0 to 63, the interpretation of the scale corresponds to *minimal anxiety* (0–7), *mild anxiety* (8–15), *moderate anxiety* (16–25) and *severe anxiety* (26–63). Previous studies have established significant reliable improvement and clinically significant change cut-points for the BAI based on normative data and comparable samples of multiple anxiety disorders [63]. As a clinician-rated assessment, we will use the **CSR of the ADIS-5** for the principal anxiety disorder. Previous studies have used the ADIS-5 as a primary outcome measure for mixed anxiety disorders (e.g., [64]).

##### Secondary outcome measures

As secondary outcome measures with the ADIS-5, we will examine **high end-state functioning** as a post-treatment CSR of “2” or lower and **treatment responder status** as a post-treatment CSR < 4.

Participants also complete diagnostic-specific measures, quality of life and functioning measures, as well as other questionnaires related to anxiety disorders. The **Social Phobia Inventory** (SPIN) [65, 66] consists of 17 items measuring the fear, avoidance, and physiological discomfort commonly experienced by people with social anxiety disorder. Each item receives a rating from 0 to 4, with higher ratings indicating higher levels of distress associated with each statement. This questionnaire has good internal reliability, test-retest reliability, convergent validity, and a cut-of score of 19 can distinguish between patients with and without social anxiety with 79% accuracy [65]. The **Penn State Worry Questionnaire** (PSWQ) [67, 68] is a 16-item questionnaire to assess the trait of worry, which characterizes generalized anxiety disorder (GAD). Patients are asked to rate how well statements about worry describe themselves from 1 to 5. If the statement does not describe them at all, it is given a rating value of 1, whereas a statement that is very typical of them would receive a rating value of 5. It assesses the trait of worry with high internal consistency and test-retest reliability. The **Panic Disorder Severity Scale Self Report** (PDSS-SR) [69, 70] asks respondents to indicate the severity of each of 7 dimensions of panic disorder during the last week on a scale from 0 to 4. A zero indicates that the patient did not experience the item and four indicates the most severe reaction. This self-report scale has good internal reliability, test-retest reliability and sensitivity to change [70]. The **Mobility Inventory for Agoraphobia** (MIA) [71] assesses the frequency of agoraphobic avoidance behaviour by asking patients to evaluate their level of avoidance of 27 places or situations when alone or when with a companion. Each item is given a rating from 1 to 5 where 1 represents no avoidance and a 5 means that the place or situation is always avoided. The MIA has been proven to have excellent internal consistency, and strong convergent and discriminant validity [71]. The **Patient Health Questionnaire** (PHQ-9) [72] is used for the assessment of the frequency of depressive symptoms with good reliability and validity. Patients indicate how many days in the last 2 weeks they have experienced any of 9 symptoms of depression with responses ranging from 0, meaning never, to 3 meaning almost every day. Scores below 10 indicate unlikely major depression while scores above 15 indicate likely major depression. The **Insomnia Severity Index** [73, 74] is a brief 7-item questionnaire assessing the severity of insomnia and associated difficulties. Each item is rated on a 0 to 4 scale, total score ranging from 0 to 28, with a higher score suggesting more severe insomnia. The instrument has been shown to have adequate internal consistency, concurrent validity documented by significant correlations with sleep diary and polysomnography measures. The **Sheehan Disability Scale** [75] is a measure that allows patients to indicate their level of disability visually, numerically, or descriptively on a scale for each of 3 life dimensions: work, social life and family life. Each item is scored from 0 being no impairment, to a 10 being extremely impaired. It is a brief rating scale that has good sensitivity and a score of 5 or higher corresponds with an increased risk of psychiatric impairment. The **EuroQoL EQ-5D** [76] is a 5-item standardised scale measuring health-related quality of life on five dimensions (e.g., mobility, self-care, anxiety/depression), each rated on 5 levels of impairment. The instrument includes a visual analogue scale to rate health from 0 to 100. The scale has excellent test-retest reliability; and good concurrent validity with the SF-36. The **Centers for Disease Control Healthy Days Measures** (CDC HRQOL-4) [77] includes one item of the perception of one’s health and three items assessing the number of days in the past 30 days when physical or mental health was not good and that activity limitations were present. The scale has demonstrated acceptable test-retest reliability and strong internal validity. The list of 21 chronic diseases from the **Disease Burden Morbidity Assessment** [78, 79] was included to document the presence of chronic conditions. The ratings of the interference of conditions on daily activities were not included. The **Mental Health Continuum Short Form** (MHC-SF) [80] consists of 14 items measuring the frequency at which respondents experience emotional, psychological, and social well-being in the past month. Items are rated from 0 (Never) to 5 (Every day). The short form of the MHC has shown excellent internal consistency, construct and discriminant validity. The **Mental Health Self-Management Questionnaire** (MHSQ) [81] assesses the use of mental health self-management strategies. It comprises 18 items rated on a 5-point Likert scale ranging from 0 (Never) to 5 (Very often), with a total maximum score of 72. The scale has satisfactory internal reliability and construct validity, adequate test–retest reliability and its convergent and concurrent validity are supported. The **Medical Outcomes Study Social Support Survey** (MOS-SSS) [82, 83] is a 6-item version of the original MOS scale which assesses the types of support and their availability on a scale from 1 (None of the time) to 5 (All of the time). The instrument has strong internal consistency and scale reliability.

#### Questionnaires completed during therapy sessions

At the onset of each session, participants complete the **Anxiety Disorder Diagnostic Questionnaire - weekly** (ADDQ-W) [84], a version adapted from the original ADDQ [85] for session-to-session transdiagnostic assessment of change in clinical fear and anxiety. The ADDQ-W possesses strong internal consistency. After sessions 3 and 9, the participants and therapists complete the 12-item versions of the **Working Alliance Inventory (WAI)** to assess the quality of the therapeutic relationship [86, 87]. The two short-form versions of the WAI include 12 items rated on a scale ranging from 1 (Never) to 7 (Always), a greater score reflecting a better alliance. The WAI is widely used in psychotherapy, and possess established construct validity and high internal consistency [88]. After sessions 1 and 12, participants complete the 6-item **Credibility Expectancy Questionnaire** [89] which assesses their perceptions of the improvement they think and feel will occur (session 1) and that did occur (session 12). The CEQ possesses high test-retest reliability high internal consistency. After the ninth session, participants complete the **Gross Cohesion Scale** (GCS) [90], a 9-item scale evaluating the perceived cohesiveness and bond among group members. The scale has acceptable reliability and validity.

For each participant, the therapists record the following information after each session: presence, homework completion, participation level, and clinical observations. The logbook content provides a better understanding of therapists’ experience, add to the evaluation of therapeutic integrity, and contribute to the optimization of the program for future large-scale implementation of tCBT. The therapists also complete a brief questionnaire comprising sociodemographic questions, items on academic and professional backgrounds, as well as experience with CBT, group therapy and treatment of anxiety disorders.

#### Linkages with administrative data

Health care utilization data will be obtained retrospectively from provincial administrative databases (e.g., computerized database of the *Régie de l’assurance-maladie du Québec* (RAMQ) for medical services, hospitalization’s registry, and medication data) after the 12 month follow-up (T_4_).

#### Sample size

It was not feasible to estimate the sample size required for a mixed regression model as current guidelines are only generalizable to particular data conditions and model structures [91]. Therefore, as an alternative, we calculated sample size for a univariate comparison for each of the primary outcomes (symptoms of anxiety as measured with the BAI and the ADIS-5) between the two study groups at post-treatment. The sample size calculation is based on a conservative estimated effect size of the intervention (Cohen’s *d*) of 0.45 at T_1_, according to previous studies [28, 34, 45, 64, 92, 93]. From pilot trial data, we estimated the correlation between the two primary outcomes to be approximately 0.7. To minimize the type-1 error associated with multiple primary endpoints, the common alpha value of 5% was adjusted to 0.03 [94]. A sample size of 182 individuals will therefore be required to detect a minimal important difference between the CBT and TAU groups, assuming an 80% power, and two-tail tests. The sample size was calculated using G*Power.

With an estimated 15% rate of loss at follow up factored in, the proposed final sample size is thus 215 patients in total (107 and 108 for each arm respectively). Such sample size will give us sufficient power to detect differences in the primary outcomes from a longitudinal perspective.

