#### Interventions

##### Group tCBT for anxiety disorders plus treatment-as-usual (TAU)

The experimental condition is the transdiagnostic group cognitive-behaviour therapy (tCBT) program published by [name] (2012) [49]. The tCBT intervention encompasses four components: 1- *Education and self-monitoring:* education on the nature of anxiety and its treatment, and introduction to self-monitoring of triggers and responses to anxiety-provoking stimuli; 2- *Specific cognitive restructuring:* thinking errors and automatic thoughts associated with anxiety; 3- *Graduated exposure and response prevention:* gradual confrontation of fear-provoking stimuli; 4- *Generalized cognitive restructuring:* examining core beliefs and perceptions of everyday life. Table 1 presents the outline of the protocol. A written treatment protocol guides the delivery of the groups for the therapists. Patients receive a tCBT workbook at the first treatment session. The tCBT group includes weekly 2-h sessions with 8–10 patients during a 12-week period. A brief telephone or face-to-face individual preliminary contact is established with each participant by one of the co-therapists during the 2 weeks prior to the first session of tCBT to introduce the treatment and build an exposure hierarchy.

**Table 1 Tab1:** tCBT treatment components

Components	Strategies
Psychoeducation (1.5 sessions)	Components of anxiety
	Treatment rationale
	Causes of anxiety
	Daily self-monitoring
Cognitive Restructuring (1.5 sessions)	Identify anxiety thoughts
	Identify misinterpretations and misappraisals
	Challenge and develop balanced interpretation or appraisal
Exposure (6 sessions)	Develop Fear Hierarchy
	Conduct in-session and homework exposure while engaging in response prevention
Schema-Based Cognitive Restructuring (2 sessions)	Identical to previous Cognitive Restructuring, but emphasis on general neurotic style
	The “tendency to interpret neutral or ambiguous stimuli as negative, threatening, and personally relevant”
Termination/Relapse Prevention (1 session)	Continued self-exposure and cognitive restructuring
	Lapses vs. relapses
	Emergency Action Plans

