#### Statistical analyses for primary outcome measures

##### Clinical outcomes

Statistical analysis of the data will follow intention-to-treat principles [101], i.e. “1) keep participants in the intervention group to which they were randomized, regardless of the intervention they actually received; 2) measure outcome data on all participants; 3) include all randomized participants in the analysis.” Baseline sociodemographic and clinical status (type of anxiety disorder, comorbidity, symptom severity, functional status, current treatment) will be described by intervention group. A mixed effects regression model will be used to account for between- and within-subject variations in the longitudinal effects of the intervention on the primary outcome measures of anxiety. Such model will allow for the inclusion of patients with missing data at any of the follow-up interviews as well as the within effect of intervention (maintenance of gains within individuals). The effects of treatment will also be adjusted for three covariates: a) comorbid depressive symptoms (continuous; PHQ-9 score); b) psychotropic medication (yes or no); c) specific anxiety disorder (ADIS-5). This set of variables will be added to the mixed regression model described above to better understand the additive contribution of each variable to the relationship between the study groups and anxiety. Functioning and quality of life outcomes also measured longitudinally will be analyzed in a similar fashion (a generalized estimating equation (GEE) with a logit-link function regression model will be used when necessary). Sub-group analyses for the presence of an antidepressant and/or benzodiazepines medication, the principal anxiety disorder at baseline and gender are planned. Treatment effect sizes will be calculated with Cohen’s d for each sub-group of interest. Compliance rates (number of sessions completed) will be compared using t-tests. Additionally, sensitivity analysis [102] will be conducted to assess the impact of missing data on estimates of treatment effects with an adequate multiple imputation statistical technique [102] and without imputation (i.e. available case analyses), as well as for outlying observations and “per protocol”. Reporting of sensitivity analysis will provide valuable information on the robustness of results.

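### tCBT is delivered in therapy groups of 8–10, but the sample size and the mixed model as described treat patients as independent, so the 80% power is optimistic and standard errors are too small if within-group outcomes correlate

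*Protocol article*

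**What the plan says.** **Design and delivery.** Trial design sets 1:1 allocation of individuals. Under Interventions, "The tCBT group includes weekly 2-h sessions with 8–10 patients during a 12-week period". Each group is led by two therapists, a primary therapist and a co-therapist chosen by managers at the site. TAU patients continue usual care and are not treated in study groups.

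**Sample size.** The article explains that sizing a mixed model was not feasible, and so "we calculated sample size for a univariate comparison for each of the primary outcomes", at post-treatment. The inputs are Cohen's d of 0.45; "the common alpha value of 5% was adjusted to 0.03" to allow for two primary outcomes; and "assuming an 80% power, and two-tail tests". The conclusion is that "A sample size of 182 individuals will therefore be required to detect a minimal important difference between the CBT and TAU groups". An allowance for 15% loss raises this to 215. The section ends by saying that this number gives sufficient power in the longitudinal perspective too. It mentions no ICC, design effect or therapist effect.

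**Analysis.** Under Clinical outcomes, "A mixed effects regression model will be used to account for between- and within-subject variations in the longitudinal effects of the intervention". Three patient-level covariates are added: PHQ-9 score, psychotropic medication and specific anxiety disorder. The sensitivity analyses cover missing data, outliers and per-protocol status. None concerns clustering by therapy group.

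**The concern.** This is a partially nested design. Patients in one tCBT group share sessions, fellow members and both therapists for 12 weeks, so their outcomes can be correlated; TAU outcomes have no such structure. The trial itself measures group cohesion after the ninth session, so some influence of the group is anticipated.

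A patient-level random effect captures correlation between repeated measures on one patient. It does not capture correlation between different patients in the same group. If that correlation is positive and the model has no term for it, the standard error of the treatment effect is too small and the test rejects too often, for both the BAI and the ADIS-5 CSR. The alpha of 0.03 was chosen to protect two primary outcomes, and this would erode that protection. A sample size that assumes independence also overstates power for the comparison it was computed on.

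**Working it through.** **Inputs from the Sample size section:** d = 0.45 (SD 1 on the standardised scale), two-sided alpha 0.03, 80% power, 15% loss. **From Interventions:** groups of 8–10, tCBT arm only. **Assumed, because the article gives none:** ICC 0.01–0.10.

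**1. Reproduce the plan's figure.** A two-sample t-test (noncentral t) with these inputs needs 91 per arm, 182 in total, with power 80.1%. Then 182 / 0.85 = 214.1, rounded up to 215. Both figures match, so independence was assumed and the only inflation is for loss. The normal formula gives 90 per arm and, at 91 per arm, 80.7% power.

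**2. Power with correlation in the tCBT arm only.** For m patients per group:

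- design effect DE = 1 + (m − 1) × ICC
- SE = √(DE/91 + 1/91)
- power = Φ(0.45/SE − 2.170), where 2.170 is the 0.985 normal quantile

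Example, m = 8 and ICC 0.05: DE = 1.35; SE = √(2.35/91) = 0.1607; 0.45/0.1607 = 2.800; Φ(0.630) = 73.6%.

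| ICC | DE (m = 8 to 10) | Power, normal formula | Evaluable N for 80% | Recruited N (÷ 0.85) |
|---|---|---|---|---|
| 0.01 | 1.07–1.09 | 79% | 186–188 | 219–222 |
| 0.02 | 1.14–1.18 | 77–78% | 192–196 | 226–231 |
| 0.05 | 1.35–1.45 | 72–74% | 212–220 | 250–259 |
| 0.10 | 1.70–1.90 | 64–67% | 242–260 | 285–306 |

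The required N per arm is (DE + 1)(2.170 + 0.842)²/0.45², rounded up. There is almost no slack: by this formula power falls below 80% once the ICC exceeds about 0.004–0.005. If losses thin the groups to about 7 analysed patients, power is about 79%, 78%, 75% and 69% across the same four ICCs.

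**3. Power of a test that respects the groups.** Simulation with 91 per arm, 11 tCBT groups of 8 or 9 analysed patients, and a cluster-mean test with Satterthwaite degrees of freedom gives about 76%, 74%, 69% and 62% at ICC 0.01, 0.02, 0.05 and 0.10. The same test reaches only about 77–78% at ICC 0, because it works with fewer degrees of freedom. That part of the gap from 80% is not due to correlation.

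**4. Type I error if groups are ignored.** The true SE exceeds the model's SE by √((DE + 1)/2). For m = 8 and ICC 0.05 this is √1.175 = 1.084, and 2 × (1 − Φ(2.170/1.084)) = 0.045. Simulation with 11 groups gives about 0.033, 0.036, 0.046 and 0.065 at the four ICCs, against the nominal 0.03.

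**The case against.** **The article is silent rather than explicit about the model.** It lists no random effects in full, and a condensed article may leave them to an analysis plan that is not shown. This stands as a limit: the standard-error point applies to the model as described, and a group term elsewhere would answer it. The sample size is different, because its assumption and its 80% are fixed in the article.

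**The 80% refers to a stand-in analysis.** The article says so and calls d = 0.45 conservative. The planned model is longitudinal, and baseline adjustment could recover power. With an assumed baseline correlation of 0.5 and small-sample degrees of freedom, power is about 85%, 80% and 71% at ICC 0.02, 0.05 and 0.10; with 0.3 it is about 78%, 73% and 65%. The article neither gives such a correlation nor makes the argument. More precision also does not correct standard errors from a model that lacks the group term.

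**The ICC is unknown.** This stands. At 0.01 the normal formula loses only one or two points.

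**Stronger readings that the document does not support.** A reader might infer that the tCBT arm carries only as much information as its number of groups. That would need an ICC of 1. At m = 8 the effective size is 91/DE, about 80, 67 and 54 patients at ICC 0.02, 0.05 and 0.10; the number of groups limits the degrees of freedom. A reader might also take group membership to be fixed throughout, but the article does not say whether it was.

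**Conclusion.** The point holds, conditional on a positive ICC. The sample size makes no allowance for group delivery, and the model as described has no level for it. Over an assumed ICC of 0.01–0.10, with 91 evaluable per arm and groups of 8–10, power for the post-treatment comparison runs from about 79% down to 64–67% by the normal formula, or from about 76% to 62% with the cluster-mean test. If the group effect is omitted, the per-outcome type I error runs from about 0.033 to 0.065 instead of 0.03. For a positive ICC, the error favours declaring superiority.

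It would go too far to say that the planned longitudinal analysis certainly lacks 80% power, or that its type I error is certainly inflated. The first depends on the ICC and on the gain from baseline and repeated measures, the second on the ICC and on whether a group term is specified elsewhere.

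**What to change.** - Add a random effect for therapy group, present in the tCBT arm only (a partially nested model), with Satterthwaite or Kenward-Roger degrees of freedom. Apply it to the BAI, the CSR and the secondary outcomes, and make an equivalent allowance where a GEE with logit link is used.
- Report the estimated ICC for each primary outcome.
- Replace the flat 80% with power at the fixed 215 over a stated ICC range, as in the table above. If credit is taken for baseline or repeated measures, state the assumed correlation and its source.

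**Cost.** Enrolment is complete, so the number of patients cannot change and need not. Group membership should be available from delivery, since therapists record attendance at each session. The price is revised analysis wording, wider confidence intervals and a less favourable power statement.
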